#### Angiographic Definition of Extension and Localization of CAD

Based on angiography, we will classify IHD patients as follows: (1) ischemia with obstructive CAD, that is, ≥ 50% diameter stenosis; and (2) ischemia with no obstructive CAD (INOCA) < 50% diameter stenosis [17]. Based on the location of the CAD obstruction, we will identify one-vessel disease (1VD), two-vessel disease (2VD), and three-vessel disease or left main coronary artery disease (3VD) groups.

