### Beyond Epicardial Obstructive Coronary Artery Disease, Microvascular Dysfunction, and its Assessment

Microvascular perfusion impairment, not explained by an epicardial critical stenosis, is a common finding in IHD and it appears to provide an adjunctive prognostic value in IHD patients [15, 16]. Therefore, the term coronary microvascular dysfunction (CMD) was coined to provide an overarching definition that encompasses different clinical scenarios. The conundrum of CMD ranges from a reduced coronary flow reserve not explained by a flow-limiting epicardial stenosis to the coronary microvascular impairment coexisting with coronary artery disease (CAD). Specifically, CMD can be detected in IHD patients with obstructive CAD undergoing urgent (reperfusion CMD) or elective PCI (interventional CMD), as well as in cases of ischemia and no obstructive CAD (INOCA) [17]. CMD can only be indirectly assessed using invasive and noninvasive techniques that measure parameters strongly dependent on the functional and structural integrity of coronary microcirculation [18]. In the coronary catheterization laboratory, CMD is commonly diagnosed by evaluating coronary blood flow before and after administration of adenosine with a Doppler-tipped guide wire in the coronary artery [19]. However, the corrected thrombolysis in myocardial infarction (TIMI) frame count (cTFC) and myocardial blush grade (MBG) provide easy and accessible angiographic indexes of coronary blood flow that do not require additional coronary artery instrumentation [20]. The intra- and inter-observer reproducibility of cTFC and MBG is acceptable, and dye injection rate and catheter size do not affect its measurement [21, 22]. It is noteworthy that cTFC and MBG have been shown to correlate with other invasive and non-invasive measures of coronary blood flow [23–26]. The cTFC, used as a surrogate marker of coronary blood velocity, predicts coronary microvascular status [27]. Interestingly, abnormal cTFC and MBG have also been related to worse prognosis, although mostly in patients with ACS [28–30]. No association between cTFC and major adverse cardiovascular events (MACE) except angina hospitalization was reported in a pilot study of Women’s Ischemia Syndrome evaluation considering 298 patients with INOCA (defined as no stenosis ≥ 50% in any epicardial vessel), but the study population included only women [31]. Therefore, it remains unclear whether the prognostic implications of an abnormal cTFC or MBG vary in different categories of male and female patients with IHD-for example, in patients varying in clinical presentation, coronary anatomy, or type/extension of coronary lesions.

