**Table 1 Tab1:**
[figure not shown]
EVA Study design

A registry will be built up of men and women aged 18 and older with suspected IHD who were referred to the catheterization laboratory in order to undergo coronary angiography and/or PCI. Patients will be recruited according to the eligibility criteria reported in Table 2. Therefore, the EVA study population will include patients with stable CAD, patients with non-ST elevation (NSTE) ACS, and patients with ST elevation myocardial infarction (STEMI).

**Table 2 Tab2:** EVA study population eligibility criteria

Inclusion criteria	Exclusion criteria
▪ Patients with ischemic heart disease (acute or chronic) undergoing percutaneous coronary intervention (urgent or elective) ▪ Written informed consent ▪ Both sexes ▪ Aged more than 18 years	▪ Life expectancy less than 12 months ▪ Active cancer (i.e., chemotherapy or ≤ 5 years from diagnosis) ▪ Pregnancy ▪ Previous coronary artery bypass graft ▪ Documented moderate–severe valvular heart disease ▪ Biological or mechanical valves

The study will be conducted in full conformance with the principles of the Declaration of Helsinki, the laws and regulations of Italy, or whichever affords the greater protection to the individual. The study has obtained the required authorization by the local Ethics Committee of Policlinico Umberto I, Sapienza University of Rome (reference 3786, 24/09/2015). Written informed consent will be obtained from all patients.

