Among the study population, we will select (1) patients undergoing urgent PCI, specifically subjects who presented within 12 h of the onset of chest pain, who had ST segment elevation of more than 0.1 mV in two contiguous leads, and for whom the clinical decision was made to treat with PCI (STEMI); (2) patients with NSTE ACS defined by acute chest pain but no persistent ST segment elevation. ECG changes may include transient ST segment elevation, persistent or transient ST segment depression, T-wave inversion, flat T waves, or pseudo-normalization of T waves or the ECG may be normal. Myocardial ischemia can occur with (myocardial infarction–NSTEMI) or without cell loss (unstable angina); (3) patients undergoing coronary angiography and elective PCI for stable angina, with stress test inducible myocardial ischemia and de novo native coronary lesion with a stenosis of less 50% (no obstructive CAD) or > 50% stenosis in any epicardial artery (mono-vessel obstructive CAD). Patients will be treated according to standard guidelines based on the CAD type, either with PCI or coronary artery bypass graft.

The recruitment phase started in April 2016 and, currently, 200 patients have already been included in the study.

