### Clinical, Pharmacological, and Gender-Related Factors

We will record complete information regarding (1) anthropometric data including height, weight, blood pressure, and heart rate; (2) socioeconomic status and gender-related factors: marital status, education level, income, physical activity (self-administered questionnaire), independent functional status Duke Activity Status Index [70], alcohol intake, smoking habits, perceived stress at work and at home, personality traits, and psychosocial characteristics and support [12, 71]; (3) cardiovascular risk factors (including familiar history of cardiovascular disease; hypertension; dyslipidemia, diabetes, previous cardiovascular events including previous MI and prior stent implantation); (4) symptom evaluation through standardized questionnaires [72, 73]; (5) dietary habits [74]; and (6) pharmacological therapy and Morisky Medication Adherence Scale—4 Items [75].

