### Statistical Analysis Plan

The data will be analyzed by appropriate statistics. Student’s *t* test and Pearson correlation will be used for normally distributed variables. When necessary, log transformation will be used to normalize the data, or appropriate non-parametric tests will be employed (Mann–Whitney *U* test and Spearman rank correlation test). Adjusted multivariate analyses will be used to assess the differences and relationships between angiographic, laboratory, and clinical characteristics, stratifying the analysis on sex- and gender-related variables. Among the pre-specified subgroup analyses, we will explore the clinical presentation of ischemia (stable vs. acute coronary syndrome), the type of disease (obstructive vs. non-obstructive disease), traditional cardiovascular risk factors, medication adherence, and the gender construct including gender identity, gender role, gender relations, and institutionalized gender. We will consider the interaction term between sex and hormones in the changes of platelet biomarkers and angiographic index of coronary flow.

All calculations will be made using appropriate statistical software packages.

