#### Sample Size Calculation

Preliminary data reported a higher rate of pathologic post-procedural MBG in women (50%) compared to men (30%) despite a TIMI flow grade 3 after PCI [80].

Therefore, the study requires 186 patients (93 per group, ratio men/women 1:1) to detect a difference of 20% in MBG < 2 at baseline and after PCI between men and women, with an alpha error equal to 5% and a power of 80%. Considering a drop-out rate of around 10%, total sample size required is 210 (105 per group).

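### INOCA is defined by a stenosis below 50% at the index angiogram alone, so patients with previously stented obstructive CAD can enter the non-obstructive class and blur the disease-type analyses

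*Protocol article*

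**What the plan says.** All places are in the protocol article.

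- **Angiographic Definition of Extension and Localization of CAD.** The rule has two classes: "Based on angiography, we will classify IHD patients as follows: (1) ischemia with obstructive CAD, that is, ≥ 50% diameter stenosis", and "ischemia with no obstructive CAD (INOCA) < 50% diameter stenosis". Neither class carries a condition on earlier revascularization.
- **Table 2 (eligibility).** The only earlier revascularization that excludes a patient is "Previous coronary artery bypass graft". Earlier PCI is not listed.
- **Clinical, Pharmacological, and Gender-Related Factors.** Baseline data include "previous cardiovascular events including previous MI and prior stent implantation", so previously stented patients are expected in the cohort.
- **Study Design and Population.** The stable-angina group is described by a "de novo native coronary lesion with a stenosis of less 50% (no obstructive CAD" or by one above 50%. The NSTE ACS and STEMI groups carry no such wording.
- **Statistical Analysis Plan.** One of the pre-specified subgroups to be explored is "the type of disease (obstructive vs. non-obstructive disease".
- **EVA Research Hypothesis and Aims, third objective.** Platelet function is compared between men and women according to CMD and CAD type.

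**The concern.** The rule describes the lumen on the day of the index angiogram, not the patient's coronary disease. A stenosis that was stented earlier and is now open reads as below 50%, so the patient joins those who never had obstructive disease. Blush and frame count in a stented territory can be abnormal because of the old disease or the old procedure, whereas the INOCA label implies microvascular dysfunction without obstructive disease.

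Two things are at stake. First, the contrast between obstructive and non-obstructive disease is diluted, whatever the sex mix. Second, if prior stents are more common in one sex, that sex's INOCA group holds more treated obstructive disease, and a sex difference in CMD within INOCA can appear, or be hidden, for that reason alone.

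**Working it through.** **1. The plan's own figure.** *Sample Size Calculation* plans on a "higher rate of pathologic post-procedural MBG in women (50%) compared to men (30"%, with alpha 5% and power 80%. For two proportions, two-sided, without continuity correction:

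n per group = [1.96 × √(2 × 0.40 × 0.60) + 0.842 × √(0.50 × 0.50 + 0.30 × 0.70)]² / 0.20² = (1.358 + 0.571)² / 0.04 ≈ 93.

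This gives 186 in total, as stated. For 10% drop-out, 186 / 0.9 = 207 (or 104 per group, 208); the stated 210 is close. The calculation concerns all men against all women and does not use the disease class, so the present point leaves it unchanged.

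**2. Who can be misassigned.**

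| Group | Can a patient with a patent stent and < 50% stenosis be classed INOCA? |
|---|---|
| STEMI | Rarely: the group is selected on a decision to treat with PCI |
| NSTE ACS | Yes: no wording on lesion type or stent history |
| Stable angina | Yes, if the stent is in another segment: the de novo native wording describes the lesion, not the patient's history |

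*Coronary Angiography Assessment* has the angiograms read by a core laboratory blinded to patient data. The recorded stent history therefore has to be brought in at analysis, and no stated rule does so.

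**3. How many (assumed; the documents give neither share).** If 10-30% of 210 patients are labelled INOCA, that is 21 to 63. If 5-30% of those have a prior patent stent, the count runs from 21 × 0.05 ≈ 1 to 63 × 0.30 ≈ 19.

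**4. Dilution of the disease-type contrast.** Let C be the true difference in CMD rate between obstructive CAD and INOCA, and f the share of labelled INOCA patients who behave like obstructive CAD. Observed contrast = (1 − f) × C. With C assumed at 20 points:

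| f | Observed contrast (points) |
|---|---|
| 5% | 19 |
| 10% | 18 |
| 20% | 16 |
| 30% | 14 |

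This needs no sex imbalance.

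**5. Spurious sex gap within labelled INOCA.** Assume CMD in 30% of true INOCA in both sexes, in 45-60% of those with a prior stent, and prior stents in 20-40% of men and 10-15% of women in the class.

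CMD rate in a sex = p × CMD_stent + (1 − p) × 0.30, so

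gap (men − women) = (p_men − p_women) × (CMD_stent − 0.30).

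- Smallest: (0.20 − 0.15) × (0.45 − 0.30) = 0.05 × 0.15 = 0.75 points.
- Largest: (0.40 − 0.10) × (0.60 − 0.30) = 0.30 × 0.30 = 9 points.
- Intermediate example: with stents in 30% of men and 10% of women and CMD_stent 50%, men 0.30 × 0.50 + 0.70 × 0.30 = 36%; women 0.10 × 0.50 + 0.90 × 0.30 = 32%; gap 4 points.
- Equal stent shares: gap 0. More stents in women: the sign reverses.

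**6. Against sampling error.** With 21 to 63 labelled INOCA patients split evenly (about 10 to 31 per sex) and CMD at 30%, the 95% half-width for a sex difference is 1.96 × √(2 × 0.30 × 0.70 / n): about 40 points at n = 10 and 23 points at n = 31.

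**The case against.** **The article condenses a fuller protocol, and the source it cites for INOCA cannot be seen.** Handling of stented patients might be settled there. That would answer a complaint that detail is missing. Here, however, the article states the classification rule itself, and as stated it labels these patients INOCA.

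**The rationale contradicts the rule.** A reader might infer this, because the section on microvascular dysfunction says that "CMD can be detected in IHD patients with obstructive CAD undergoing urgent (reperfusion CMD) or elective PCI (interventional CMD") and lists INOCA separately. The documents do not support it. That sentence concerns a current procedure, not an old stent, and the same section reports a cited study that defined INOCA by stenosis alone. Treated obstructive CAD fits poorly with the category described there, but there is no contradiction.

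**The exposure is narrow.** This largely stands. Most STEMI patients fall outside the problem, and the de novo native wording removes stable patients whose only lesion is the stented segment.

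**Adjustment can deal with it.** Prior stent is recorded and adjusted analyses are planned. Adjustment does not correct a class label, though, and the subgroup would still be formed by the stenosis-only rule.

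**The effect is small beside the noise.** This stands for the sex contrast within INOCA, where the half-width of 23 to 40 points far exceeds a bias of 0.75 to 9 points. It limits the weight of the point; it does not justify a label that mixes two kinds of patient.

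**Removing stents leaves earlier MI without a stent in INOCA.** This also stands, as a limit of the remedy.

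**Conclusion.** The point holds in a limited form. The stated rule admits patients with previously stented obstructive CAD to the non-obstructive class, mainly NSTE ACS patients and stable patients with a stent in another segment. What it can affect is the exploratory disease-type subgroup, the CAD-type comparison in the third objective, and the sex contrast within INOCA.

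A reader might infer that the main result is compromised, or that the bias must run against the study hypothesis. Neither follows. The primary men-women comparison does not use this class, and the direction of any sex bias depends on which sex has more prior stents, which the documents do not say. The 0.75 to 9 points, the dilution figures and the patient counts all rest on assumed inputs. It is a cheap improvement worth making before analysis, not a threat to the trial's main conclusion.

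**What to change.** For the disease-type analyses, define INOCA as stenosis below 50% in all vessels and no prior stent. Put patients with < 50% stenosis and a prior stent in a separate class, known treated obstructive CAD, and keep them out of the non-obstructive arm of the subgroup and of the CAD-type comparison. Report the stenosis-only rule as a sensitivity analysis, and give the number of prior-stent patients by sex so that the extent of the problem is visible.

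The cost is one sentence in the classification section and one extra class. The variable is already collected, so no new data are needed; this matters because 200 patients of the planned 210 were already included when the article was written. The downside is a somewhat smaller INOCA subgroup: by 1 to 19 patients under the assumptions in step 3.

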### Laboratory Measurements

Routine blood tests (e.g., cardiac troponin, as myocardial injury index, whole blood count, creatinine level, glycemia, lipid profile, hepatic enzymes) performed during hospitalization will be recorded.

The collection of biological samples for studies of platelet function will be performed in accordance with the guidelines suggested by the international literature and at scheduled time points. Blood samples will be properly maintained until batch analysis in freezers at − 80 °C. All samples will be coded to ensure anonymity and entered in conjunction with clinical data in a computerized database protected by double access code/password. All assays will be performed in a blinded fashion. The samples analyzed by immunoassay methods will be tested in duplicate, and those with concentrations exceeding the standard curve will be assayed again after appropriate dilution. The results obtained will be compared with reference values obtained in our laboratory on a reference population (healthy subjects, both sexes, and aged from 25 to 80 years).

During the angiography, blood samples will be collected at coronary and peripheral levels before and after PCI. According to a previously reported study, the arterial sample will be suitable for testing biomarkers of platelet function [77]. Moreover, a peripheral sample collection after 24 h will be performed.

Given the close interaction between thrombosis and hormone pathways, we plan to evaluate experimental biochemical markers of platelet function in association with sex hormone profiles.

In every patient, regardless of sex, we will perform the measurement of 17-beta estradiol (E2), luteinizing hormone (LH), follicle-stimulating hormone (FSH), and free testosterone (BioT). The BioT/E2 ratio will be calculated. For women, we will consider for the interpretation of results data concerning the menopausal status and, if in pre-menopause, the timing of the menstrual cycle in which the blood collection was performed.

To better understand sex differences, plasma, serum, and cell lysates opportunely prepared from the enrolled populations will be collected and managed in an appropriate manner. Furthermore, the platelet-rich plasma will be prepared for the study of platelet aggregation, and in vivo markers of platelet activation (i.e., thromboxane, soluble CD40 ligand, soluble P selectin, isoprostanes) will be detected. Apoptotic processes, protein expression of estrogens and androgens, and their signaling will all be measured in the cell lysates. Platelets will be used to study signal transduction pathways of sexual hormone receptors, nitric oxide synthase (NOS) phosphorylation, and oxidative stress pathways including NADPH oxidase 2 (NOX2). In these cell types, the protein expression of endocellular and membrane receptors will also be studied using Western blot. The involvement of the receptors will be investigated using specific inhibitors, hormones, and specific agonists.

Using flow cytometry, we will analyze platelet-derived microparticles and surface receptors (i.e., CD40 ligand, P-selectin, GPIIb/IIIa, CX3CR1, GPVI) from resting and activated platelets in vitro of patients with ACS versus age- and sex-matched healthy individuals. Therefore, we could evaluate the correlation between circulating molecules and membrane-associated markers.

### CMR Sub-Study

With the aim of better describing the CMR pattern of CMD in IHD patients, we planned a pilot study including (1) patients (*N* = 10; ratio W/M = 1:1) with mono-vessel obstructive CAD undergoing PCI and (2) patients (*N* = 10; ratio W/M = 1:1) undergoing angiography that documented no obstructive coronary disease with an impairment of microvascular dysfunction defined during angiography by a MBG < 2. Exclusion criteria will be (1) standard contraindication to magnetic resonance; (2) severe arrhythmia or tachycardia; (3) history or evidence of systemic autoimmune disorders, sarcoidosis, amyloidosis, or congenital heart disease; and (4) chronic kidney disease stages 4 and 5 (glomerular filtration rate < 30 mL/min/1.73 m^2^).

The procedure will be performed within 7 days from angiography to detect coronary microvascular dysfunction related to the procedure according to standard protocol (i.e., first-pass perfusion and the delayed post-contrast sequences). All CMR studies will be analyzed off-line in consensus by two experienced observers blinded to clinical information, using a workstation with dedicated cardiac software.

### Follow-Up Phase

The follow up-phase will include the in-hospital length of stay and 1 year after discharge. A phone call interview within 3 months and an ambulatory visit at 12 months will be performed.

Clinical, pharmacological, and behavioral information will be re-assessed at the time of follow-up. Information concerning the duration of in-hospital stay as well as any adverse events before discharge will be collected. The letter of discharge for each participant will be collected. Reassessment of medication adherence, as well as psychosocial and behavioral aspects will be checked at the scheduled follow-up as well as the occurrence of new comorbidities.

Adverse clinical outcomes will be determined through the medical chart reviews following the index angiography. Peri-procedural and after-discharge complications with focus on thrombotic and bleeding events will be recorded. Minor and major bleeding events according to International Society on Thrombosis and Hemostasis [78] and Bleeding Academic Research Consortium [79], as well as recurrence of angina symptoms will also be recorded during the follow-up phase.

All participants will be followed for 1 year to verify clinical endpoints: early (30 days) and late mortality (12 months) for cardiac-related events or for any other cause; recurrence of acute coronary syndrome; need for re-interventions or coronary artery bypass graft, complications related to PCI or re-admission for cardiac-related cause (i.e., heart failure), or for any other causes.

### Data Collection, Management, and Quality Assurance

The EVA coordination group ([name], [name], [name], [name]) will have full access to data and they will be responsible for the data management, including quality check. Investigators will be responsible for data entry into the electronic case report forms (eCRFs). In case of discrepant data, the coordination group will request data clarification, and if this should not be sufficient, the patient will be excluded from the analysis. EVA collaborators will receive training and a have access to a checklist for appropriate eCRF completion. By using a validation plan integrated in the data entry software, data will be checked for missing or contradictory entries and values out of the normal range. A final database will be created and validated by the study coordinator. Patients’ identification names will be registered by recruiting personnel. A series of consecutive numbers will identify patients. Regular monthly meetings will be conducted to check the sustainability of the project.

Source documents (paper or electronic) in which patient data are recorded will be collected. They will include, but not be limited to, hospital records, clinical and office charts, laboratory notes, patient-reported outcomes, evaluation checklists, pharmacy dispensing records, copies of transcriptions that are certified after verification as being accurate and complete, patient files with radiological images, and records kept at medico-technical departments involved in the trial. Source documents, required to verify the validity and completeness of data, must be retained per the policy for retention of records.

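### An unresolved data discrepancy removes the whole patient, with no limit to the affected item or analysis, which risks selective exclusion and some loss of power

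*Protocol article*

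**What the plan says.** Under Data Collection, Management, and Quality Assurance, the protocol article gives a two-step rule for discrepant data. The coordination group first asks for clarification; "if this should not be sufficient, the patient will be excluded from the analysis". The section does not define a discrepancy, does not restrict the rule to particular variables, and does not restrict the exclusion to analyses that need the doubtful item.

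The same section says that the coordination group "will have full access to data and they will be responsible for the data management, including quality check". Through the entry software, "data will be checked for missing or contradictory entries and values out of the normal range". It also describes training, a checklist for completing the case report form, and collection of source documents.

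Blinding is stated for the angiographic core laboratory (Coronary Angiography Assessment), for the assays (Laboratory Measurements) and for the magnetic resonance readers (CMR Sub-Study). None is stated for the exclusion decision.

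Under Sample Size Calculation, 186 evaluable patients (93 per sex) are required "to detect a difference of 20% in MBG < 2 at baseline and after PCI between men and women". The only allowance for losses is: "Considering a drop-out rate of around 10%, total sample size required is 210 (105 per group"). Drop-out is not defined there.

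**The concern.** The case report form is wide. Besides angiography and laboratory data it holds income, education, stress, personality traits, diet, physical activity and medication adherence, and much of this is collected again at follow-up. Under the rule as written, one contradictory answer that a query cannot settle, in diet or income for example, takes the patient out of the analysis, even when MBG, sex, hormones and 12-month outcome are all sound. An error in one item becomes the loss of a patient.

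Two things could be at stake:

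- **Selection.** Many of these items are self-reported, and the gender-related ones are exposures of interest in the analysis plan. A late query is also harder to settle for a patient who has died, and mortality is an endpoint. If unresolved discrepancies are related to sex, gender factors or outcome, the patients left no longer represent the cohort, and the comparison of men and women can shift in either direction. The group making the decision is not stated to be kept from the data being compared.
- **Power.** No separate allowance for data exclusions is named, and the margin above the required 186 is small once the full 10% drop-out has occurred.

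**Working it through.** **Inputs.** From Sample Size Calculation: MBG < 2 in 50% of women and 30% of men, alpha 5% (taken as two-sided, which reproduces the stated figure), power 80%, 93 per group, drop-out about 10%, 210 in total (105 per group). The rate of unresolved discrepancies is not in the documents, so every exclusion rate below is an assumption.

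**1. The plan's own figure.** Pooled two-proportion formula without continuity correction:

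n = [1.96·√(2·0.40·0.60) + 0.842·√(0.50·0.50 + 0.30·0.70)]² / 0.20² = 93.0 per group, or 186 in total.

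This matches. For drop-out, 186/0.90 = 206.7, so 207; the stated 210 is slightly more generous.

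**2. Margin.** If the full 10% drops out, 210 × 0.90 = 189 remain, which is 3 more than 186 (3/189 = 1.6%). If nobody has dropped out before MBG is read, the margin is 210 − 186 = 24 patients (24/210 = 11.4%).

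**3. Power after random exclusion of a share x**, with the same formula:

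| Extra exclusion x | Beyond the 10% drop-out: n per group = 105 × 0.90 × (1 − x) | Power | From all 210: n per group = 105 × (1 − x) | Power |
|---|---|---|---|---|
| 0% | 94.5 | 0.81 | 105 | 0.85 |
| 5% | 89.8 | 0.79 | 99.8 | 0.83 |
| 10% | 85.1 | 0.76 | 94.5 | 0.81 |
| 15% | 80.3 | 0.74 | – | – |

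On the first reading, power falls below 80% once more than about 1.6% are excluded. On the second it stays at or above 80% up to about 11%.

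**4. Selective exclusion, for illustration.** Start from 94.5 per group after drop-out, exclude a share e of women and no men, and let a share q of the excluded women have MBG < 2. The observed rate in women is (0.50 − e·q)/(1 − e).

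- e = 10%, q = 70%: (0.50 − 0.07)/0.90 = 47.8%. The difference falls from 20 to 17.8 points, and power with 85 women and 94.5 men is about 0.69.
- e = 2%, q = 70%: (0.50 − 0.014)/0.98 = 49.6%. Power is about 0.79.
- e = 10%, q = 30%: (0.50 − 0.03)/0.90 = 52.2%. The difference rises to 22.2 points, so the same rule can also exaggerate the contrast.

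The first and third cases differ only in who is excluded. Each moves the difference by 2.2 points, in opposite directions, and nothing in the documents says which case is nearer the truth.

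**The case against.** The strongest case for the plan has five parts.

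- **Exclusion is the last step.** Training, a checklist, built-in validation, clarification requests and source documents come first and should keep unresolved cases few. This is fair. It bears on how often the rule bites, not on what the rule does when it bites.
- **Missing is not discrepant.** The exclusion clause concerns discrepant data; missing entries appear in a separate sentence about software checks, with no exclusion attached. Death, transfer or an incomplete questionnaire mainly produce missing data. This stands: a reader might infer that missing items also remove the patient, but the article does not say so.
- **The 10% may cover data exclusions.** Drop-out is undefined, and loss during the 12-month follow-up would not remove an MBG value obtained at the index procedure. This also stands, which is why both readings are in the table. That exclusions come on top of the 10% is an inference.
- **No bias is shown.** A reader might conclude that the rule biases the comparison of the sexes and the 12-month analysis, or that exclusions are decided with outcomes in view. The documents support neither as fact. They give no rate or direction of unresolved discrepancies. Full data access with no stated blinding permits an informed exclusion but does not establish one, and MBG reading itself is blinded to patient data.
- **Detail belongs elsewhere.** Imputation methods and reporting tables are commonly left to a fuller plan that is not shown, and their absence is no fault here.

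What remains is the rule itself. It is stated affirmatively and at patient level, so a fuller plan that kept these patients would contradict it.

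**Conclusion.** The point holds as a badly fixed rule that creates a risk. Followed as written, it discards valid primary and outcome data because of an unrelated doubtful item, and it leaves patient-level exclusion to a group not stated to be blinded.

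Its effect cannot be sized from the documents. On the assumption of random exclusion of 5% to 15% beyond a full 10% drop-out, power goes from 0.81 to between 0.79 and 0.74. On the equally tenable assumption that the 10% allowance is available for data exclusions, about 11% can be lost before power falls below 80%. Selective exclusion could matter more than lost numbers, but its presence, direction and size are unknown.

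Selection is the main reason to change the rule; the power loss is secondary and depends on how drop-out is read. This should be fixed, but it is not a flaw that by itself invalidates the study.

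**What to change.** Replace the exclusion clause in Data Collection, Management, and Quality Assurance with:

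*An unresolved discrepant value is set to missing for that item only; the patient stays in every analysis for which the required data are valid; the decision is made without knowledge of MBG/cTFC and outcome.*

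If the sponsor intended something narrower than the present wording, such as exclusion only when a key variable cannot be verified, the text should say so. Because 200 patients were already included when the article was written, the change should be made before the database is finalised.

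The cost is one sentence, denominators that vary between analyses, and some routine handling of missing data. No extra patients or procedures are needed.
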